However, there are no data at present to support the efficacy of CP treatment in MERS-CoV infection; therefore, it has been recommended to administer CP only in the context of a clinical trial. While an RCT will be required to evaluate effectiveness, evaluating effectiveness on clinical endpoints such as mortality will likely require several hundred to several thousand seriously ill MERS-CoV patients in order to achieve sufficient statistical power, anticipating reasonable potential effect sizes. Additionally, CP from different MERS-CoV survivors will likely contain differing levels of neutralizing anti-MERS-CoV antibodies. Since seriously ill MERS-CoV-infected patients may have detectable viral RNA in various locations that can be sampled (for example lower respiratory tract secretions) for prolonged periods, it might be possible to first determine the relationship between neutralizing antibody dose and antiviral effects on clinical and laboratory features in a small open-label study. This information would be very helpful to design of an RCT and in determining the most appropriate neutralizing antibody dose, or dosing range for the study. This may also inform dose selection for follow-on anti-MERS-CoV antibody preparations currently in pre-clinical development (for example, neutralizing human monoclonal antibodies, polyclonal human neutralizing immunoglobulin derived from transchromosomic cattle (personal communication, [name]).

Therefore, we plan to conduct a 2-phase study. In the first phase (CP collection phase), we will explore the feasibility of collection of CP from donors who have significant titers of anti-MERS-CoV antibodies. In the second phase, patients with MERS-CoV infection will be treated with CP. If the protocol is feasible, safe, and associated with temporal changes in viral load and illness, this pilot study will inform a larger concealed intervention, placebo-controlled RCT that is powered to evaluate efficacy of CP on relevant clinical outcomes.

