### Statistical and analytical plan

#### Sample size calculation

This is an exploratory study, aimed at rectifying the current lack of information on the use of CP to treat MERS-CoV infection. Due to the exploratory nature of this study and the paucity of sequential data on viral RNA levels in respiratory tract and blood samples from MERS-CoV-infected patients, and on their clinical progress, the sample size is fixed at 20, which is a realistic target for a study of 12 months duration. The sample size of 20 is sufficient to reach a conclusion that the 28-day survival rate significantly exceeds 60 % (p = 0.032, 2-sided) if 17 or more patients survive for the 28 days of follow-up. This would represent promising evidence to motivate a full-scale comparative clinical trial.

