#### Analysis of clinical data

The SOFA score and indicators of whether the patient requires organ support via oxygen and ventilation, dialysis or vasopressors will be plotted against time.The relationships between the SOFA score at day 3 and the neutralizing antibody dose received, and between receipt of any type of organ support during the 28 days of observation and the neutralizing antibody dose received, will be characterised by fitting a logistic regression model to the data from the 20 treated patients. The log viral load at baseline will be included in these models.The vital status (alive or dead) of each patient will be recorded for all days 0–28. The proportion alive will be plotted against time.The relationship between the hazard of death and the neutralizing antibody dose received will be characterised by fitting a Cox proportional hazards regression model to the data from the 20 treated patients. The log viral load at baseline will be included in this model.The probability of a patient dying on or before 28 days will be estimated by the proportion of the 20 treated patients for whom this occurs. An exact, conservative, two-sided confidence interval for this probability will be calculated using the method of Clopper and Pearson (1934).The time from infection/exposure and sample collection in days, duration from infection/exposure to CP therapy, length of stay in ICU; the number of ICU-free days; the duration of mechanical ventilation; the numbers of ventilator-free days, of renal replacement therapy-free days, and of vasopressor-free days; and the length of stay in hospital will be presented as histograms, and suitable summary statistics will be computed.

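### The Cox model of death on antibody dose rests on about 8 deaths at the plan's null survival and at most 3 if the survival mark is met; a penalised fit, labelled descriptive, would be a cheap improvement

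*Protocol article*

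**What the plan says.** The Sample size calculation section of the protocol article states that "the sample size is fixed at 20, which is a realistic target for a study of 12 months duration". It justifies this number by a test of 28-day survival against 60%, with a two-sided p of 0.032 "if 17 or more patients survive for the 28 days of follow-up". The same section says: "This is an exploratory study, aimed at rectifying the current lack of information on the use of CP to treat MERS-CoV infection".

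Under Analysis of clinical data, the plan follows death daily: "The vital status (alive or dead) of each patient will be recorded for all days 0–28". It then models it: "The relationship between the hazard of death and the neutralizing antibody dose received will be characterised by fitting a Cox proportional hazards regression model", and adds: "The log viral load at baseline will be included in this model". The model therefore has two covariates. The article names no estimator for it, gives no expected number of deaths, and says nothing about what happens if deaths are few.

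The Background hopes that a small open-label study can relate antibody dose to antiviral effects on clinical and laboratory features, and says of this: "This information would be very helpful to design of an RCT and in determining the most appropriate neutralizing antibody dose".

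**The concern.** The plan's survival mark and its dose-mortality model pull in opposite directions. The better the survival, the fewer the deaths, and a Cox model draws its information from deaths. With two covariates and a handful of events, maximum partial likelihood has known small-sample faults: estimates too far from zero on average when a true effect exists, model standard errors that are too small, and occasional infinite estimates.

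The dose relationships are meant to feed into planning of the later randomised trial. A very large hazard ratio resting on two or three deaths could be taken there as a finding when it is largely noise.

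**Working it through.** **Inputs from the protocol article.** Sample size 20, reference survival 60%, mark of 17 or more survivors and p = 0.032 (Sample size calculation); two covariates and 28 days of follow-up (Analysis of clinical data). The article gives no covariate distributions and no effect sizes, so those used below are assumptions.

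**1. The plan's own figure.** With X the number of survivors, P(X ≥ 17 | n = 20, 0.60) = 0.01596. Doubled, this is 0.0319, which rounds to the stated 0.032. With 16 survivors the doubled p is 0.102, so 17 is the correct threshold.

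**2. Number of deaths.**
- At 60% survival: 20 × (1 − 0.60) = 8 deaths, or 8 / 2 = 4 per covariate. The binomial SD is √(20 × 0.4 × 0.6) = 2.2, and the chance of 5 to 11 deaths is 89%.
- With 17 or more survivors: at most 20 − 17 = 3 deaths, or at most 3 / 2 = 1.5 per covariate.

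**3. How likely 3 or fewer deaths are.** The binomial probability is 1.6% if true survival is 60%, 11% at 70%, 41% at 80% and 70% at 86%.

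**4. Best-case precision.** For a standardised covariate, SE(log HR) ≈ 1/√D, where D is the number of deaths. The hazard ratio per SD detectable with 80% power is then exp(2.8/√D): exp(2.8/√8) = 2.7 and exp(2.8/√3) = 5.0.

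**5. Simulation of the usual Cox estimate.** Assumptions: n = 20, independent normal covariates, true hazard ratio 0.6 per SD of dose (log −0.51) and 1.5 per SD of baseline load, number of deaths held fixed, estimates bounded at ±5 on the log scale. Ranges are across repeated runs.

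| | 8 deaths | 3 deaths |
|---|---|---|
| Mean log HR (true −0.51) | −0.62 | −0.72 to −0.76 |
| RMSE | 0.55 to 0.56 | 1.16 to 1.19 |
| Beyond 5-fold per SD | 4 to 4.5% | 14 to 17% |
| Wrong sign | 9% | 21 to 22% |

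The mean overstatement is 0.62/0.51, about 20%, at 8 deaths, and 0.72/0.51 to 0.76/0.51, about 40 to 50%, at 3. The median at 8 deaths is −0.56 to −0.57, about 10% too large. With 2 deaths, 25 to 27% of estimates are beyond 5-fold. With 1 death, about a third are infinite.

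**6. Other assumed effects.** With a true log hazard ratio for dose of −0.405 or −0.693, and 0.405 or 0.693 for viral load:
- At 8 deaths the mean is 16 to 20% too large. The actual SD is 0.52 to 0.60, against a median model SE of 0.42 to 0.46.
- At 3 deaths the mean is 43 to 51% too large. The actual SD is 1.2 to 1.4, against a median model SE of 0.72 to 0.79, and 1 to 4% of fits diverge.
- With no true effect the mean is about zero, but 3% of fits at 8 deaths and 18% at 3 deaths still show more than a 3-fold hazard ratio per SD.

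**7. The same model with Firth's penalty.** Under the assumptions of step 5, RMSE falls from 0.55–0.56 to 0.49–0.51 at 8 deaths, and from 1.16–1.19 to 0.85–0.86 at 3. Estimates beyond 5-fold at 3 deaths fall to 8–9%. The wrong-sign rates do not change. With true log hazard ratios of −0.693 for dose and 0.405 for viral load, the mean at 3 deaths moves from −0.93 (after dropping the 3% of fits that diverged) to −0.76, and every penalised fit is finite.

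**The case against.** - **The article does not name the estimator.** A penalised Cox model is still a Cox model, and a separate analysis plan could specify it. This stands in so far as the plan contains no wrong figure and no contradiction. But the article does fix the model, both covariates and the population, and an unqualified Cox fit is normally the unpenalised one.
- **Exaggeration at any number of deaths.** A reader might infer that the estimates will be badly inflated whatever happens. The calculations do not support this. At 8 deaths the problem is mainly imprecision, and with no true effect there is no directional bias at all. The severe case needs 3 or fewer deaths, which has a 1.6% chance at 60% survival and becomes common only if survival is about 80% or more.
- **60% as a forecast.** A reader might take 8 as the number of deaths the plan predicts. The 60% is only the value the survival test is set against.
- **The hazard ratio as the dose-setting result.** A reader might infer that it alone will select the antibody dose for the randomised trial. No section says so. The model carries no test or decision rule, two viral-load models also address dose, and the Discussion says that the therapy phase is not designed to establish efficacy. Still, the Background and Conclusions count clinical features or endpoints among the dose relationships that should inform that trial.
- **The penalty as a rescue.** It is not one. It improves RMSE only modestly at 8 deaths, and the sign is wrong equally often with or without it.

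**Conclusion.** The point holds as a cheap improvement to one exploratory model, not as an error in the plan. The event counts, 8 at the null reference and at most 3 at the survival mark, follow directly from the plan's figures. At about 8 deaths the usual estimate is imprecise and mildly exaggerated. At 3 or fewer it is unstable, exaggerated on average, and reported with standard errors well below its true scatter.

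The sizes rest on independent normal covariates and assumed effect sizes. Skewed or correlated covariates would probably make the fit less stable. The RMSE figures also depend on bounding the estimates at ±5.

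**What to change.** In Analysis of clinical data, keep the same Cox model and covariates, but fit it by Firth's penalised partial likelihood and report profile-likelihood confidence intervals. Both are available in SAS and R, which the plan already names. Add wording such as: the hazard ratio is descriptive; when deaths are very few, the antibody dose and survival time of each patient who died are presented beside it. A fixed cut-off, such as 3 deaths, may be stated but is not essential.

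The cost is one option in the model statement and a sentence or two of text, with no extra patients. The downside is slight shrinkage of the hazard ratio toward 1. Because the change restores neither power nor the correct sign, the descriptive label is needed as well as the penalty.

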### Stratified analyses

We will conduct exploratory stratified analyes based on (1) the time between symptom onset and CP therapy initiation, (2) comorbidities, (3) co-intervention; and (4) baseline severity (SOFA scores) at treatment initiation.

The SAS System for Windows version 9.3 (SAS Institute, Inc., Cary, North Carolina) and R will be used for all analyses.

### Discussion and current status

This protocol was developed collaboratively by King Abdullah International Medical Research Center (KAIMRC), Gulf Cooperation Council (GCC) Infection Control Center Group and the World Health Organization—International Severe Acute Respiratory and Emerging Infection Consortium (ISARIC-WHO) MERS-CoV Working Group. It was approved by the Ministry of the National Guard Health Affairs Institutional Review Board (IRB) (approval number IRBC/13/244, 5th June 18, 2014) and has been registered at clinicaltrials.gov (NCT02190799).

If proven effective, CP therapy is an attractive therapeutic option for MERS-CoV infection. Besides the biologic plausibility of this therapy, it is easy to obtain and administer, relatively inexpensive, and is likely to be acceptable to patients and treating teams. Side effects are unlikely to differ from those of transfusion of any other fresh frozen plasma. We believe this study protocol sets the stage to a large efficacy trial.

The strengths and weaknesses of the study protocol should be noted. In the CP collection phase subjects will be enrolled from 4 different cohorts, in order to explore all potential donors. It is unknown, at this point, which subjects are likely to have high antibody titers and therefore be CP donors. We are hoping that this feasibility study will help identifying a group of superdonors who have very high titers. By identifying the characteristics of such individuals, a more focused approach for donation can be followed. The CP therapy phase is not designed to establish efficacy; such objective requires an adequately powered randomized controlled trial. However, we believe performing this feasibility study is an essential step to examine the safety, clinical and laboratory effects and the pharmacokinetics of the MERS-CoV antibody response. The study involves giving critically ill patients this therapy in a controlled monitored setting. However, a recent systematic review suggested that early treatment with CP is likely to be more effective than late treatment (Mair-Jenkins et al. 2015). Therefore, if the feasibility study shows that CP is safe and feasible, the next step should be a randomized controlled trial that is sufficiently powered to detect effect on mortality and enrolls patients early in the course of the disease.

## Conclusions

Our study is anticipated to provide information about the feasibility of collecting convalescent plasma in large quantities for therapeutic use in a large numbers of MERS-CoV patients. The data is anticipated to inform about the relation between the antibody titers in the CP and viral clearance and other laboratory and clinical endpoints. This data will be critical in planning a larger RCT to examine the efficacy of CP on patients with MERS-CoV infection.

## Abbreviations

MERS-CoV: Middle East respiratory syndrome coronavirus
ICU: Intensive care unit
PCR: Polymerase chain reaction
ISARIC: International Severe Acute Respiratory and Emerging Infection Consortium
SARS: Severe acute respiratory syndrome
CP: Convalescent plasma
HCW: Health care workers
WHO: World Health Organization
ELISA: Enzyme linked immunosorbent assay
IFA: Indirect fluorescent antibody
